### Outcome measures

#### Sick leave

The primary outcome measure is defined as: duration of sick leave in calendar days from the first day of sick leave to full return to work, lasting at least 4 weeks without (partial or full) relapse. Variables of the rehabilitation process itself, like the time to first (partial or full) return to work, total days of sick leave in the whole year, and (partial or full) return to work rates after 2, 6 and 12 months, are secondary outcome measures. Sick leave in the past year is considered to be a prognostic factor for our primary outcome measure, as are job content data [21,22].

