#### Reduction of SMD symptoms

An important secondary outcome measure is reduction in symptoms of depression, anxiety, somatization and distress, measured with the 4DSQ [18]. Life-events and problems, chronic illnesses and neuroticism [23] are prognostic measures for this outcome. Problem evaluation [24] and coping styles [25] are measured to evaluate the effective components of the MISS: problem- and solution focus skills of patients.

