### Power & sample size

Proportions used to determine the sample size needed, were adopted from a related study completed in the occupational health care setting [13]. In that study, after a period of 3 months 79% in the intervention group versus 64% in the control group had fully returned to work. In order to detect a relevant difference in survival analysis on our primary outcome measure, nQuery Advisor [30] was used to calculate the sample size. With a power of 80% at a 0.05 level two-sided log-rank test for equality of survival curves between the MISS group proportion still on sick leave of 0.21 and a usual care group proportion of 0.36 at the given time of 3 months, the sample size needed in each group was 126 (with a constant hazard ratio of 1.528). Taking into account an intracluster correlation coefficient (ICC) of .025 (clustering effect in our groups is not presumed to be large) for randomisation at GP level and 7 patients per cluster (GP), a total of 290 patients are needed. Assuming a dropout rate of 30% (approximately 10% at each follow up), inclusion of a total of 415 patients is necessary.

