### Statistical methods

First of all, baseline similarity between the MISS and usual care groups will be examined, and baseline characteristics of drop outs and completers will be compared. Cox regression analyses will be used to investigate the intervention effect, by analysing differences in outcome with survival analysis of the primary outcome measure between the MISS and usual care group. To correct for misclassification of patients and severity of complaints (inclusion is only by level of distress with sick leave), and as a consequence to avoid bias in the effect, baseline measures of psychological symptoms (by means of the 4DSQ [31] & PRIME-MD [32]), as well as medical records will be examined. Additionally, subgroup analysis can be done by level of severity of complaints.

Linear and logistic multilevel analyses will be used to investigate the intervention effect on all secondary outcome measures: rates of return to work, psychological symptoms, problem experience and coping style. Also, longitudinal multivariate analysis will be used to examine differences in improvement in all secondary outcome measures between the treatment groups. Analysis will be performed on an intention-to-treat basis and intra-class-correlation will be calculated to correct for possible clustering of observations. Levels included will be: repeated measures, patients and GPs. Subgroups for analysis will be modelled by the prognostic factors mentioned.

Costs will be measured and valued from a societal perspective. Mean direct and indirect medical costs (measured with the Tic-P[26]), costs of productivity loss due to sick leave (measured with the WHO HPQ[28]) and total costs will be compared between both groups. Confidence intervals around mean differences will be estimated with bootstrapping methods. With regard tot the primary outcome, sick leave, a cost benefit analysis will be performed, in which costs of productivity loss due to sick leave will be compared with direct en indirect medical costs.

A cost-effectiveness analysis will be performed to assess the incremental costs per unit improvement on the 4DSQ [18]. Bootstrapping methods will be used to estimate the confidence interval for the cost-effectiveness ratio and to a draw cost-effectiveness plane. Similarly, utility assessed with the EuroQol [29] will be used to estimates the incremental costs per Qualy gained in a cost-utility analysis.

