As regards the prognostic measures, univariate analyses will be used to select relevant factors, with a focus on identifying prognostic factors for our primary outcome measure. Subsequently, Cox regression analyses and logistic regression analysis will be performed on these relevant factors.

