### Prospect on outcomes

Notably, effectiveness instead of efficacy is studied. We are evaluating what is possible in real clinical practice, rather than under ideal circumstances. As a consequence, mental health state will vary between the participants. Through subgroup analysis on severity of complaints and levels of distress (measured with the PRIME-MD and 4DSQ), we can classify possible high or low risk groups for prolonged disability within this heterogeneous group. Identification of a high risk group for non-recovery may lead to better suited guidelines on stepped care and treatment. We cannot assure that everyone in the MISS group has received the intervention; the GPs were given total freedom in actually delivering the MISS. Nevertheless, the number of visits, diagnoses, recommendations, treatments and proceedings will give us information about the compliance of the GPs and their influence on the effect of the MISS. In this way, daily practice is measured in stead of ideal circumstances. To avoid social desirable answers from the GPs on their advises and treatments, we will also check the medical records of the patients.

Finally, many requirements for a high quality trial are being met. Results of this cluster RCT will contribute to treatment options for patients having SMDs with sick leave in general practice, and might contribute to new and better suited guidelines and stepped care. Results will be available in the end of 2006.

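### Univariate screening of prognostic factors can drop real factors and keep proxies; for the Cox model on sick leave, the expected number of events makes it avoidable

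*Protocol article*

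**What the plan says.** The last paragraph of Statistical methods in the Protocol article sets out two steps for the prognostic measures. First, "univariate analyses will be used to select relevant factors, with a focus on identifying prognostic factors for our primary outcome measure". Then: "Subsequently, Cox regression analyses and logistic regression analysis will be performed on these relevant factors". Factors that fail the first step do not reach the second.

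The candidates are spread over three places:
- Under Sick leave: "Sick leave in the past year is considered to be a prognostic factor for our primary outcome measure, as are job content data".
- Under Reduction of SMD symptoms: "Life-events and problems, chronic illnesses and neuroticism [23] are prognostic measures for this outcome". Here the outcome meant is symptoms, not sick leave. The same section measures problem evaluation and coping to study how the intervention works, and does not call them prognostic.
- Under Statistical methods: baseline 4DSQ and PRIME-MD scores are to be examined as measures of severity.

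The article gives neither a total number of candidate parameters nor an expected event count for this analysis.

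**The concern.** Distress, depression, anxiety, neuroticism, problems and life events are likely to be correlated. Looking at such factors one at a time has three weaknesses:
- A factor whose effect is masked by a correlated factor can look irrelevant alone and be discarded, although it would show once the other is adjusted for.
- A factor with no effect of its own can pass because it stands in for one that has an effect.
- The second-step models treat the surviving factors as if they had been fixed in advance, so their coefficients and p-values tend to look better than they should.

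Factors bearing on sick leave and return to work are part of what the one-year follow-up is meant to assess (Objective). What is at stake is whether the reported list names the right factors and whether their strength is stated fairly.

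**Working it through.** **1. The plan's own sample size, as a check on the inputs** (Power & sample size). The article sizes the trial "With a power of 80% at a 0.05 level two-sided log-rank test", with 0.21 and 0.36 still on sick leave at 3 months.
- Hazard ratio: ln(0.21)/ln(0.36) = 1.528, as stated.
- Freedman events: ((1.528 + 1)/(1.528 − 1))² × (1.960 + 0.842)² ≈ 180.
- Mean event probability: 1 − (0.21 + 0.36)/2 = 0.715. Then 180/0.715 ≈ 252, or 126 per group, as stated. The unrounded hazard ratio gives 127.
- Design effect: 1 + (7 − 1) × 0.025 = 1.15. Then 252 × 1.15 = 289.8, so 290, as stated.
- Dropout: 290/0.70 = 414.3, so 415, as stated.

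**2. Events available to a prognostic Cox model.** Patients enrolled: 433 (Patients); less 30% dropout, 433 × 0.70 = 303. The Background cites earlier research in which about 20% were off work for more than a year. If that share applies here, about 80% have the event by 12 months.

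| Patients | Event share | Events | Parameters at 10 events each | At 20 events each |
|---|---|---|---|---|
| 290 | 0.715 | 207 | 20 | 10 |
| 303 | 0.715 | 217 | 21 | 10 |
| 303 | 0.80 | 242 | 24 | 12 |
| 433 | 0.80 | 346 | 34 | 17 |

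The last row assumes no dropout. The rules of 10 and 20 events per parameter are working conventions, not figures from the article.

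**3. Candidate parameters (assumed).** Past-year sick leave 1, job content scales about 2 to 8, and life events, problems, chronic illnesses and neuroticism about 4: in all 7 to 13. Adding the 4DSQ, PRIME-MD and treatment arm gives about 14 to 20. At 10 events per parameter both sets fit in every row. At 20, the narrow set mostly fits and the wide set only partly.

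**4. What the screen can do (assumed entry level p<0.05).**
- A single real factor passes with probability Φ(√E × ln HR − 1.96). With E = 217 events and HR 1.15 per SD: √217 = 14.73, ln 1.15 = 0.140, so Φ(0.10) = 0.54 and the factor is dropped 46% of the time. With HR 1.20 it is dropped 23% of the time. In a joint model it would stay in, with its estimate and interval.
- Simulation with 15 candidates, 80% events and 150 runs. Two real factors correlate at 0.5 and have opposite effects (log HR ±0.25 per SD). A proxy with no effect of its own correlates at 0.6 with a real factor (log HR 0.3).

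| N | Masked factor dropped by screen | Same factor non-significant in full model | Proxy kept by screen | Proxy significant in full model |
|---|---|---|---|---|
| 303 | 61% | 10% | 67% | 7% |
| 433 | 46% | 2% | 83% | 5% |

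The Monte Carlo standard error near 67% is √(0.67 × 0.33/150) ≈ 4 percentage points. The correlations and effects are chosen to show the mechanism; they are not taken from the article. The screen columns describe the first step only: a proxy that passes may still lose its effect in the second step if the factor it stands for has passed too.

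**5. Logistic models.** The article does not say at which time point these apply. For 12-month return the smaller outcome group sets the limit: 290 × 0.20 = 58, 303 × 0.20 = 61, 433 × 0.20 = 87 non-returners. At 10 each that is 5 to 8 parameters.

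**The case against.** Much can fairly be said for the plan.

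- **A condensed article leaves detail to other documents.** This stands for the entry threshold, shrinkage and validation, and their absence is not held against the plan. The selection rule itself is stated, however, and an analysis plan that followed it would carry the same weakness.
- **Clustering and treatment arm.** A reader might infer that the screen ignores both. The text does not say so, and Statistical methods plans a correction for clustering with GPs as a level.
- **Consequences for guidelines.** The article hopes that "Identification of a high risk group for non-recovery may lead to better suited guidelines on stepped care and treatment", and a reader might infer that the screen builds this group. It does not: the same section forms risk groups by severity on the PRIME-MD and 4DSQ, so the link to the screen is at most indirect.
- **Chance findings.** With 12 to 15 independent null candidates, the probability that at least one passes at p<0.05 is 1 − 0.95¹² = 46% to 1 − 0.95¹⁵ = 54%. Testing the same null coefficients in one full model gives about the same figure, so it does not count against screening in particular.
- **Certainty of the harm.** It would be tempting to say that the screen does drop real factors and keep false ones. The article supports only that it can; how often depends on correlations and effects that it does not report.
- **All candidates in one model.** This holds for the Cox model up to about 20 parameters. It fails for a 12-month logistic model, and would fail for a much longer list of subscales.

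**Conclusion.** The point holds as a low-cost improvement to a secondary analysis. The stated rule can mislead when candidates are correlated, and its second step ignores the selection made in the first. For the Cox model on the primary outcome, 207 to 346 expected events make the screen avoidable for about 20 parameters at 10 events each. This rests on three assumptions: the 3-month rates used for planning or the cited one-year figure apply to this population; the candidates come to about 7 to 20 parameters; and 10 events per parameter is acceptable. Under a stricter 20 per parameter, the wide list would need some reduction or shrinkage.

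A reader might infer that the trial's main result is at risk. It is not: the comparison of MISS with usual care does not use this step.

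**What to change.** Replace the univariate selection step as follows.

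- **List the baseline candidates in advance:** past-year sick leave, job content, life events and problems, chronic illnesses, neuroticism, baseline 4DSQ and PRIME-MD. Leave out coping and problem evaluation unless they are declared as candidates.
- **Cox model:** fit all of these together, with treatment arm and an allowance for clustering by GP (frailty or robust errors). If a reduced model is wanted, obtain it by shrinkage or check it by bootstrap validation.
- **Logistic models of 12-month return:** reduce the list beforehand on subject-matter grounds to about 5 to 8 parameters, or penalise.
- **Univariate results:** show them as description only.

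The cost is a change of wording and some extra analysis work, with no new data. The results table will be longer and the p-values less striking.

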## Discussion

### SMDs in primary care

This project is developed for the primary care setting with its' typical case load of stress-related mental disorders, and not for specialised care in which patients have more clearly defined mental disorders. We provide an intervention that is aimed at better recognition, good communication, and a time-contingent framed recovery process. Our approach of SMDs, with the need to identify specific psychiatric disorders where they exist and also to respect the roles of daily life in determining and shaping psychological disability, is an example of specified stepped care in general practice. Potential risk factors for chronicity are pointed out in our training, and early recognition and treatment is the main goal of the MISS. The role of more specialised care is well acknowledged in the intervention.

### Benefits of our screening method

Particular strength of our study protocol is the method of recruiting patients. By using the computerised patient record system, we screened the whole population of general practice attendees and thereby determined who entered the study, instead of chartering the GPs to select their patients. Therefore, similarity in both groups is assured and we avoided selection bias. Also, we did not have difficulties in including enough eligible patients, which is often a problem in primary care trials. Furthermore, the current method allows us to consider the pragmatic effectiveness and to avoid interference with daily practice of consulting hours. In this trial, follow-up is on patients having SMDs with sick leave, instead of patients who actually get an intervention for their complaints. Good external validity (i.e. generalizability) is accomplished by this rather heterogeneous, and therefore highly representative, group of patients with SMDs on sick leave. To assure as much internal validity as possible in this pragmatic trial, we randomised on the level of GPs to avoid contamination. In addition, research assistants who collected the data and also the patients were blinded.

### Prospect on outcomes

Notably, effectiveness instead of efficacy is studied. We are evaluating what is possible in real clinical practice, rather than under ideal circumstances. As a consequence, mental health state will vary between the participants. Through subgroup analysis on severity of complaints and levels of distress (measured with the PRIME-MD and 4DSQ), we can classify possible high or low risk groups for prolonged disability within this heterogeneous group. Identification of a high risk group for non-recovery may lead to better suited guidelines on stepped care and treatment. We cannot assure that everyone in the MISS group has received the intervention; the GPs were given total freedom in actually delivering the MISS. Nevertheless, the number of visits, diagnoses, recommendations, treatments and proceedings will give us information about the compliance of the GPs and their influence on the effect of the MISS. In this way, daily practice is measured in stead of ideal circumstances. To avoid social desirable answers from the GPs on their advises and treatments, we will also check the medical records of the patients.

Finally, many requirements for a high quality trial are being met. Results of this cluster RCT will contribute to treatment options for patients having SMDs with sick leave in general practice, and might contribute to new and better suited guidelines and stepped care. Results will be available in the end of 2006.
